## Abstract

**Background:**

Low physical activity and reduced physical functioning are common after renal transplantation, resulting in a reduced quality of life. Another common post-transplantation complication is poor cardio-metabolic health, which plays a main role in long-term outcomes in renal transplant recipients (RTR). It is increasingly recognized that weight gain in the first year after transplantation, especially an increase in fat mass, is a highly common contributor to cardio-metabolic risk. The aim of this study is to compare the outcomes of usual care to the effects of exercise alone, and exercise combined with dietary counseling, on physical functioning, quality of life and post-transplantation weight gain in RTR.

**Methods:**

The Active Care after Transplantation study is a multicenter randomized controlled trial with three arms in which RTR from 3 Dutch hospitals are randomized within the first year after transplantation to usual care, to exercise intervention (3 months supervised exercise 2 times per week followed by 12 months active follow-up), or to an exercise + diet intervention, consisting of the exercise training with additional dietary counseling (12 sessions over 15 months by a renal dietician). In total, 219 participants (73 per group) will be recruited. The primary outcome is the subdomain physical functioning of quality of life, (SF-36 PF). Secondary outcomes include other evaluations of quality of life (SF-36, KDQOL-SF, EQ-5D), objective measures of physical functioning (aerobic capacity and muscle strength), level of physical activity, gain in adiposity (body fat percentage by bio-electrical impedance assessment, BMI, waist circumference), and cardiometabolic risk factors (blood pressure, lipids, glucose metabolism). Furthermore, data on renal function, medical history, medication, psychological factors (motivation, kinesiophobia, coping style), nutrition knowledge, nutrition intake, nutrition status, fatigue, work participation, process evaluation and cost-effectiveness are collected.

**Discussion:**

Evidence on the effectiveness of an exercise intervention, or an exercise + diet intervention on physical functioning, weight gain and cardiometabolic health in RTR is currently lacking. The outcomes of the present study may help to guide future evidence-based lifestyle care after renal transplantation.

**Trial registration:**

Number: NCT01047410.

**Electronic supplementary material:**

The online version of this article (10.1186/s12882-017-0709-0) contains supplementary material, which is available to authorized users.

## Background

Low physical activity, reduced physical fitness and reduced physical functioning are common after renal transplantation [1]. Physical activity levels decline already in the early stages of chronic kidney disease, and reach a nadir at end-stage renal disease [1]. This low physical activity aggravates the catabolic state that is common in patients with renal disease, which leads to deconditioning and reduced physical functioning [1]. Spontaneous recovery of physical activity level after transplantation is modest, and limited physical functioning remains common [1]. Likewise, low cardiorespiratory fitness and muscle weakness are also common after renal transplantation [1]. This may be improved with exercise and physical activity, however, RTR experience barriers to engage in exercise and physical activity such as fear of movement, lack of motivation, and fatigue [1, 2].

The incidence and prevalence of cardiovascular disease is estimated to be 4 to 6 times higher in RTR compared to the general population [3]. Various factors may explain poor post-transplantation health in RTR, including the legacy of end-organ damage due to the prior medical history (e.g. cardiovascular damage), that may not be fully reversible by restoring renal function. Importantly, the common substantial post-transplantation weight gain, which is primarily due to an increase in body fat mass, is a major trigger for the poor cardio-metabolic profile in the RTR, including post-transplant diabetes and the metabolic syndrome [4–9]. Furthermore, post-transplantation BMI is an important risk factor for graft failure and premature death [10–13]. A poor diet post-transplantation may be related to pre-transplantation dietary prescriptions such as low intake of vegetables to avoid hyperkalemia and a high intake of energy rich drinks to ensure adequate energy intake [14, 15]. Additionally, glucocorticoid use after transplantation often promotes overeating, so a healthy diet without an excess of calories is frequently required [16]. Data from a previous study showed that RTR gain an average of 5.7 ± 5.0 Kg of body weight in the first year after transplantation (Fig. 1) [4]. Interestingly, the rise in body weight was related to low physical activity and poor diet rather than increased energy intake [4].

**Fig. 1 Fig1:**
[figure not shown]
Changes in body weight and body composition after renal transplantation. (**a**: BMI, **b**: body fat percentage, **c**: fat-free mass, and **d**: whole body water content) Reprinted from “The role of diet and physical activity in post-transplant weight gain after renal transplantation” by D.M. Zelle, 2013, Clinical Transplantation, 27: E484-E490. Reprinted with permission

From the above, it may be clear that both physical activity and diet are important targets for lifestyle intervention in RTR. The importance of physical activity and exercise for health outcomes is well-acknowledged in the general population [17]. In RTR however, high level evidence on the effects of physical activity and exercise on physical functioning and cardiometabolic health is limited and comes from few small RCTs [18, 19]. The available studies however, including single group interventions, show promising results. Dietary intervention after renal transplantation was shown to reduce body weight and improve lipid profile [20], whereas intensive lifestyle intervention improved glucose metabolism [21]. Importantly, it was also shown that a supervised exercise program lead to similar improvements in muscle strength and aerobic capacity in RTR compared to healthy individuals [22].The first year after transplantation may provide a window of opportunity to improve physical functioning and quality of life, and to prevent post-transplantation weight gain and its cardiometabolic consequences. Assuming that muscle disuse is a major factor in muscle weakness and low aerobic capacity in RTR, exercise rehabilitation and increased daily physical activity may be of great benefit to this patient population. For physical activity and exercise to result in a favourable shift from a catabolic to an anabolic state, proper consideration of nutritional status, in particular energy and protein intake, and metabolic status is necessary. Furthermore, dietary counseling directed at restoring a healthy eating pattern may prevent post-transplant weight gain and improve dietary quality.

The Active Care after Transplantation (ACT) study is a pragmatic randomized controlled trial designed to evaluate the effects of an exercise intervention, and an exercise + dietary intervention, on physical functioning and quality of life after renal transplantation. In addition, detailed measures of physical fitness, level of physical activity, gain in adiposity, renal function, and cardiometabolic profile will be investigated, as well as success factors for lifestyle change in RTR. A health economics evaluation is included.

## Methods/design

Active Care After Transplantation (ACT) is a multicenter pragmatic randomized controlled trial in renal transplant patients in the Netherlands, registered on www.clinicaltrials.gov as NCT01047410. The ACT trial has three study arms: usual care versus exercise intervention versus exercise + diet intervention (Fig. 2). It is designed according to the principles of a pragmatic RCT to allow evaluation of the intervention in real-life care facilities. Details are described below according to the CONSORT statement for parallel randomized trials and the extension of the CONSORT statement for pragmatic trials [23–25]. The study is performed according to the declaration of Helsinki and ethical approval is obtained from the University Medical Center Groningen Medical Ethics committee (NL49084.042.14). Adverse- and serious adverse events data are collected and closely monitored to ensure the ongoing safety of the participants. Both are reported in a standardized Adverse Events Report Form. Exemption to report adverse events is given for common renal transplant related co-morbidities, such as cardiovascular events, urinary tract infections, viral infections, pneumonia, urine retention, rejection, cardiac decompensation, hydronephrosis, nephrostomy catheter, lymphocele, hypertension, dyslipidemia, diabetes, post-transplantation lymphoma, cerebrovascular accidents, meningitis, and skin cancer.

**Fig. 2 Fig2:**
[figure not shown]
Flowchart of the ACT trial

### Eligibility criteria

The target population for the study are adult RTR, recruited during routine post-transplantation care shortly, but at least within the first year after transplantation. Inclusion criteria are: written informed consent; age > 18 years; < 1 year after transplantation; approval for participation based on a general medical evaluation by their nephrologist. Exclusion criteria included the following: multiple organ transplantation; psychopathology or serious cognitive impairment; physical or clinical limitations that make participation impossible; pregnancy, negative screening verdict by the nephrologist or cardiologist. Participants receive a small financial reimbursement (10 Euro) for participation in the final follow-up measurement at 15 months. Participation in the exercise training sessions and dietary care are financed by research funds, and participants’ travel expenses are reimbursed. Pre-defined reasons to discontinue participation in the study included pregnancy and conversion to dialysis. Furthermore, reasons to discontinue participation are: changes in ECG during maximal aerobic capacity testing, systolic blood pressure > 250 mmHg, diastolic blood pressure > 120 mmHg or blood pressure decline of > 20 mmHg during maximal aerobic capacity testing, and severe cardio-pulmonary complaints during the exercise trainings sessions.

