### Screening, recruitment and randomization

All RTR patients are screened for eligibility during the post-transplantation recovery period, so within 7–10 days after surgery, by the nephrologist. Eligible RTR are invited to participate, informed about the study protocol and if agreed are asked to participate and sign written informed consent. In case of non-Dutch or non-English speaking patients, interpreters are used.

In total, 219 participants (73 per group) will be recruited. The sample size is based on the expected improvement on the physical functioning scale of quality of life of 13.8 points in the intervention group and 8.8 points in usual care (α=0.05, β= 0.80, SD = 11.0) [26]. A difference of 5.0 points between the standard effect is considered a relevant effect. This results in a required number of 57 RTR per group. Taking into account a potential dropout rate of 15% and a correction for heterogeneity between centers of 10%, this results in a total required number of 73 RTR per group (*N* = 219 in total). Randomization to one of the three arms is computerized using the ‘PROC SURVEYSELECT’ function in the software program SAS (Cary, North Carolina, USA). It is performed by an independent data management company hosting the data entry facility, who are not involved in conducting the study itself (Nefrovisie foundation, Utrecht, the Netherlands). Participants are randomized by block randomization in groups of 6–9 for rehabilitation centers and in groups of 3 for physiotherapy practices.

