### Usual care

Participants randomized to the usual care group receive standard post-transplant care as usual in the hospitals. Current standard nutrition care after kidney transplantation consists of 1–4 inpatient consultations by a renal dietitian during the inpatient stay (7–10 days), followed by 1 outpatient consultation. During inpatient consultations attention is paid to optimal nutritional intake, maintaining a stable body weight and muscle mass, or increasing body weight when needed. After a few months, during the outpatient follow-up, attention is paid to maintaining a stable body weight, or increasing or decreasing body weight when needed. When a participant has increased cholesterol, (un)saturated fat intake is discussed, and mono/disaccharides are discussed when a participant has increased HbA1c. Likewise, salt consumption is discussed in case of increased 24-h sodium excretion. Exercise or lifestyle counseling are not included in the standard post-transplant care in either of the participating hospitals. Participants randomized to the usual care group receive general advice to meet the standard Dutch exercise guidelines (30 min of moderate physical activity per day) and follow the Dutch Dietary guidelines.

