### Exercise only intervention

The exercise intervention consists of two phases. The first phase is a 3-month exercise training program, followed by the second phase; a 12-month active follow-up with lifestyle counseling (Figure 2). Exercise training sessions are done in groups of 4–10 participants in the rehabilitation centers and with 1–6 participants in the physiotherapy centers.

The training program encompasses two exercise training sessions per week (21 exercise training sessions and 3 test sessions in total) and is focused on improving maximal muscle strength, local muscle endurance, and aerobic capacity. Each exercise training session consists of 30-min dynamic resistance training of all the major muscle groups (Additional file 1: Table S1) using resistance training machines, 30 min of aerobic training (cycle-ergometry and treadmill walking), and is concluded with a 30-min supervised sports activity or swimming, depending on the available facilities.

The dynamic resistance training includes both maximal strength training (relatively high load, fewer repetitions), and muscle endurance training (relatively low load, large number of repetitions).

Optimal resistance training load is determined using one-repetition maximum testing (1RM) for each participant. The content of the training program is in line with the American College of Sports Medicine guidelines exercise in healthy adults [27], and was previously shown to be effective in improving muscle strength and aerobic capacity in RTR [22]. The full resistance- and aerobic training program is shown in Additional files 1 and 2: Tables S1 and S2.

Maximal muscle strength (1RM) for all exercise machines (Additional file 1: Table S1) is assessed at baseline. For maximal muscle strength training, moderate loading is used (50–60% 1RM), for 2–3 sets of 8–10 repetitions. Higher loads are known to be more appropriate for maximal muscle strength, however 50–60% 1RM is used in our protocol as most participants are untrained, and RTR have increased risk of tendon ruptures. For local muscle endurance training a light-to-moderate load is used (25–35% 1RM), for 1–3 sets of 30 repetitions. All resistance exercise involved exercise machines, no free weights are used for safety reasons.

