### Outcomes

The primary outcome is the subdomain physical functioning of quality of life of the SF-36. Secondary outcomes include other evaluations of quality of life (SF-36, KDQOL-SF, EQ-5D), muscle strength (Additional file 1: Table S1), aerobic capacity, physical activity, gain in adiposity (body fat percentage by bio-electrical impedance assessment, BMI, waist circumference), and cardiometabolic risk factors (blood pressure, lipids, glucose metabolism). Furthermore, data on renal function, medical history, medication, psychosocial factors (motivation, kinesiophobia, coping style), nutrition knowledge, nutrition intake, nutrition status, fatigue, work participation, process evaluation and cost-effectiveness are collected. Effectiveness of the diet intervention will be determined at 15 months. To study barriers and success factors regarding lifestyle counseling in RTR, data are gathered on psychological factors including motivation, kinesiophobia, and coping style. A comprehensive overview of the measurements in the ACT trial is shown in Table 1.

**Table 1 Tab1:** Overview of measurements in the ACT trial

Outcome	Method	Time points
Quality of life		T0, T3, T6, T15
Physical functioning	SF-36 PF subscale [72, 73]	
Other subdomains and total	SF-36 [72, 73]	
Renal specific	KDQOL-SF [39]	
General	EQ-5D [69]	
Physical function		
Aerobic capacity	VO_2_peak ergometer test [74]	T0, T3, T6, T15
	Sub-maximal ergometer test	T0, T3, T6, T15
Muscle strength	1RM tests for leg extension, leg curl, chest press, close-grip pull-down	T0, T3, T6, T15
Balance and mobility	Short Physical Performance Battery [41]	T0, T15
Physical activity level	Baecke questionnaire [42]	T0, T3, T6, T15
	Step counter (Yamax SW200) [75]	T0, T3, T6, T15
Body composition		
Weight, Height, WC, HC	WHO guidelines [76]	T0, T3, T6, T15
Nutritional status (undernutrition)	SGA [77]	T0, T15
Body fat percentage	BIA (Biostat Quadscan 4000, Douglas, Isle of Man)	T0, T3, T6, T15
Muscle mass	BIA (Biostat Quadscan 4000, Douglas, Isle of Man)	T0, T3, T6, T15
	24-h creatine excretion [44, 78]	T0, T3, T6, T15
Cardiometabolic risk factors		
Blood pressure	(Speidel & Keller Maxi Stabil 3)	T0, T3, T6, T15
Blood lipids	TG, TC, HDL-C, LDL-C in fasting serum levels (Cholesterol oxidase-phenol aminophenazone method, MEGA AU 510; Merck Diagnostica, Darmstadt, Germany)	T0, T3, T6, T15
Glucose metabolism		
Insulin resistance	HOMA-IR (fasting glucose, insulin)	T0, T3, T15 (all)

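### Pregnancy and conversion to dialysis end participation in the study, so questionnaire and cost follow-up stops after post-randomisation events that the intention-to-treat and 15-month cost analyses should include

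*Protocol article*

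**What the plan says.** Under Eligibility criteria, the protocol article gives two groups of reasons for stopping.

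- **First group.** "Pre-defined reasons to discontinue participation in the study included pregnancy and conversion to dialysis". The object is explicit: the study itself, not an intervention or a test.
- **Second group.** "Furthermore, reasons to discontinue participation are: changes in ECG during maximal aerobic capacity testing". The sentence goes on to blood-pressure limits at the same test and ends with "severe cardio-pulmonary complaints during the exercise trainings sessions". Here the article does not say what participation refers to.

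The same section also uses the word in a narrower sense: "Participation in the exercise training sessions and dietary care are financed by research funds".

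Outcomes and Table 1 name SF-36 physical functioning as the primary outcome. It and EQ-5D are scheduled at T0, T3, T6 and T15. Care-consumption questionnaires run at T0, T3, T6, T9, T12 and T15. Statistical analyses applies intention to treat to the primary analyses, and Health economic analysis takes a societal view over 15 months. No section shown says that questionnaires continue after any of the listed events.

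**The concern.** An intention-to-treat comparison needs outcomes on all randomised patients, including those whose course goes badly. Return to dialysis is such a course and is plausibly related to physical functioning. A rule that ends study participation at that moment means later scores are never collected, and no analysis plan can recover them. The primary outcome is a questionnaire that needs neither training nor a maximal test, so patient safety gives no reason to stop it.

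The cost analysis is exposed in the same way. Dialysis is a major health event, and the costs and utilities that follow it would be missing from the 15-month comparison.

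The second group of reasons raises a further question. Training is supplied only in the two exercise arms, and of usual care the article says: "Exercise or lifestyle counseling are not included in the standard post-transplant care in either of the participating hospitals". If severe complaints in training ended study follow-up, that reason could remove patients only from the exercise arms.

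**Working it through.** **1. What each reason does, read against the other sections**

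| Reason | Scope as written | Arms in which it can act |
|---|---|---|
| Pregnancy, conversion to dialysis | The study (explicit) | All |
| ECG or blood-pressure findings at the maximal test | Open | All: Table 1 schedules VO2peak without the asterisk that marks intervention-only measures |
| Severe cardio-pulmonary complaints in training | Open | Exercise and exercise + diet only |

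Two other sections favour a narrow reading of the open rows. Aerobic capacity uses the same ECG and blood-pressure findings only to stop the test. Statistical analyses treats completion of training as a per-protocol matter.

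**2. Visits lost**

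- Dialysis starting between T6 and T15, say at month 9: T0, T3 and T6 are kept, and 1 of 4 physical functioning scores is lost (T15). The month 12 and month 15 cost questionnaires are lost too.
- Training complaint, on the study-exit reading: "The first phase is a 3-month exercise training program, followed by the second phase". Training therefore lies between T0 and T3, so 3 of 4 scores (75%) are usually lost and only T0 remains.
- A finding at the T15 test costs no later visit. One at T0 may precede randomisation.

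**3. Precision (illustration; the loss rates are assumed)**

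Inputs from Screening, recruitment and randomization: 73 per arm, SD 11.0, dropout 15%. The plan's inflation step reproduces: 57 × 1.15 × 1.10 = 72.1, rounded up to 73. Nothing below depends on the 57.

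- Planned dropout: 0.15 × 73 = 10.95, leaving 62.05 per arm.
- Assumed loss to these rules of 2-5%: 0.02 × 73 = 1.46 and 0.05 × 73 = 3.65 patients per arm.
- Standard error of a two-arm contrast = 11 × √(2/n):
  - n = 62.05: 1.975
  - n = 62.05 − 1.46 = 60.59: 1.999 (+1.2%)
  - n = 62.05 − 3.65 = 58.40: 2.036 (+3.1%)

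If the losses fall within the 15% allowance, the increase against plan is 0. If they come on top, 1.2-3.1% is an upper bound at these rates, because it treats each affected patient as wholly lost although earlier visits stay in the mixed model.

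**4. Bias (illustration; it arises only if training complaints mean study exit)**

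In a completer analysis, bias = (share lost in the exercise arm − share lost in usual care) × deficit of those lost. The excess share (2-5%) and the deficit (11-22 points, which is 1-2 SD) are both assumed.

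- Low: 0.02 × 11 = 0.22 points, 4.4% of the 5.0-point target difference.
- High: 0.05 × 22 = 1.10 points, 22% of it.
- For a mixed model with only T0 from these patients, multiply by (1 − r), where r is the share of the deficit that T0 predicts, assumed 0-0.5. The range is 0.22 × 0.5 = 0.11 to 1.10 × 1 = 1.10 points.
- Equal losses and deficits in both arms, or the narrow reading: 0.

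**The case against.** The strongest case on the other side has four parts.

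- **The open sentence may be harmless.** It drops the explicit reference to the study that the sentence before it carries. Read with the test-stopping rule and the per-protocol definition, it fits stopping the test or the training at least as well as leaving the study. This stands. A reader might infer that the rules bias the contrast towards exercise, but the documents do not support that. It needs the wider reading, a real excess of such complaints and a large deficit, and none of these is stated. Patients are also screened by the nephrologist and take a medically supervised maximal test at T0, which makes a large excess less likely.
- **The explicit reasons can arise in every arm.** Nothing in the article suggests that training changes the rate of dialysis or pregnancy. Similar losses largely cancel in the contrast, and the sample size already allows for dropout. This stands too, and leaves mainly a loss of precision and of cost data.
- **The full protocol may provide for continued follow-up.** It may. But the article does more than stay silent: it states that these two events end participation in the study, and a centre following that sentence would stop collecting data.
- **There is some design rationale.** Weight, bio-impedance and maximal-test results are hard to interpret in pregnancy or on dialysis. That justifies dropping those measurements, not the questionnaires.

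**Conclusion.** The point holds as a minor one. The rule for pregnancy and dialysis is explicit. Followed as written, it discards physical functioning, EQ-5D and cost data after randomisation, which is inconsistent with the intention-to-treat primary analysis and truncates the 15-month cost analysis. It weakens the intention-to-treat analysis without defeating it: the patients stay in their randomised arms, and their earlier visits still contribute to the mixed model.

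The size cannot be derived from the document, which gives no event rates, and is probably small. At an assumed 2-5% loss, the standard error rises by between 0 and 3.1%. The 0.11-1.10 point bias range is illustrative only. It depends on a reading of the second sentence that the text does not settle and on assumed rates and deficits, so it should not be cited as an estimate. What can be said of that sentence is that its scope is unclear and that centres could apply it differently.

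**What to change.** Replace the two sentences with a rule that separates stopping treatment or testing from stopping follow-up. Pregnancy, dialysis conversion, test findings and training complaints end training and/or maximal testing as clinically indicated. SF-36, EQ-5D, cost questionnaires and medical-file follow-up continue to T15 unless the patient withdraws consent. Analyse these patients as randomised, and report discontinuation of training, testing and follow-up separately, with reasons, by arm. The clinical safety criteria stay as they are.

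The cost is a change of wording and a few extra questionnaires for patients who have stopped training or testing, are pregnant or have returned to dialysis.
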